## Abstract

**Background:**

There is a growing prevalence of loneliness and social isolation among older adults (OAs). These problems are often associated with depressive states, cognitive decline, sleep disorders, addictions, and increased mortality. To limit loneliness and social isolation in OAs, some authors recommend the use of new communication technologies to maintain a social link with family members as well as with health and social care professionals. Among these communication tools, telepresence robots (TRs) seem to be a promising solution. These robots offer users the possibility of making video calls with their relatives, social workers, and health care professionals, to maintain social contact and access to support services while living at home. Nevertheless, TRs have been relatively unstudied in real-life environments.

**Objective:**

The main objective of this study is to measure the impact of a 12-week intervention using a TR on the feeling of loneliness and on social isolation of OAs living at home. Its secondary objective is to establish recommendations for the implementation of TRs in the studied context.

**Methods:**

A nonrandomized study will be conducted among 60 OAs living at home who will participate in the study for 24 weeks. During this period, they will host a TR for 12 weeks to use it in their home. After the end of the intervention a 12-week follow-up ensues. In total, 4 evaluations will be performed over the entire experimental phase for each participant at weeks 0, 6, 12, and 24. A multidimensional assessment of the impact of the robot will be performed using a multimethod approach including standardized scales and a semistructured interview. This assessment will also help to identify the ergonomic aspects that influence the robot’s usability and acceptability among OAs.

**Results:**

Data collection started in September 2020 and is expected to be completed in early 2023. In August 2022, 56 participants were recruited for the study. Data analysis will take place between August 2022 and is expected to be completed in early 2023.

**Conclusions:**

The DOMIROB study will provide new knowledge on the impact of social TRs in OAs living at home. The results will make it possible to suggest technological, ethical, and organizational recommendations for the use and implementation of TRs for OAs in real-life settings.

**Trial Registration:**

ClinicalTrials.gov NCT04767100; https://clinicaltrials.gov/ct2/show/NCT04767100

**International Registered Report Identifier (IRRID):**

DERR1-10.2196/40528

## Introduction

### The Risk of Loneliness and Social Isolation Among Older Adults

Throughout the world, social isolation and loneliness among older adults (OAs) living at home has reached very high levels. In Europe, in 2018, it was estimated that around 10% of individuals aged over 75 years were socially isolated [1]. In France, in 2017, nearly 300,000 individuals over the age of 60 years experienced social withdrawal [2]. In the United States, one-quarter (25%) of the population over 65 years were socially isolated in 2020 [3]. In Canada, in 2009, 12% of the population over the age of 65 years also encountered this problem [4]. In 2019, it was estimated that about 6 million (7.62%) elderly people lived alone in Japan [5]. However, being socially isolated and experiencing a feeling of loneliness are not the same thing. A person can objectively live in a socially isolated way (ie, having a reduced social network, a lack of social contact or support) and not feel lonely, and conversely, they could not live in a context of social isolation and experience a feeling of loneliness [6]. Loneliness seems to be even more widespread than social isolation among OAs. Several studies estimate that about one-third of OAs experience a feeling of loneliness [7-9], especially after the age of 80 years, with approximately 50% of OAs reporting frequent loneliness [10].

Loneliness and social isolation have particularly harmful consequences for OAs’ psychological and physical health (depression, addictions, cognitive decline, sleep disorders, and excess mortality) [11-15]. Retirement, loss of professional contacts, widowhood, death of relatives and friends, and chronic diseases (which can limit travel) favor withdrawal and social isolation in OAs [16,17].

### New Technologies: A Socialization Solution for OAs?

Several authors have advocated interventions using technologies, such as computers, tablets, the internet, SMS text messaging and social media apps, videoconferencing, or robots, to alleviate loneliness and improve quality of life in OAs [18,19]. Digital technologies (eg, tablets, social networks, video games, and robots) can be useful to mitigate the consequences of social isolation and loneliness in OAs [19-23]. Digital tools allow users to get information through the internet, to maintain social contact with their relatives, and to improve social participation via different communication tools (eg, instant messaging and social networks). Nevertheless, the digital divide persists, notably because these technologies are not tailored to OAs’ needs and preferences. It is important that the technology is ergonomic, easy to use, and useful for this population. For example, it is recommended to use simplified interfaces and contents that meet OAs’ capacities and preferences in addition to introducing tools (eg, stands, tablet holders, stylus) that can increase the comfort and ease of use of the equipment for the individual [24]. Today, different actors from the field of innovation and digital technologies work on the development of adapted solutions to meet OAs’ needs that could minimize the digital divide. Telepresence robots (TRs) are an example. TRs are tools that help create a connection between 2 distinct environments through cameras, microphones, speakers, and a screen. TRs offer a videoconferencing functionality integrated on a navigation base with wheels that allow the robot to move around in an environment. TRs can be used to promote social contact with relatives and friends and access to a wide range of distant assistance services. Although TRs seem to have promising functionalities for the management of isolation in OAs, they remain poorly studied and deployed in home environments.

### TRs: A Solution That Has Not Been Thoroughly Studied for Seniors Living at Home

Since the beginning of the COVID-19 health crisis, different stakeholders have shown an increasing interest in innovative remote communication solutions and TRs [25-38]. However, thus far, there is limited available evidence concerning the implementation and usefulness of TRs in a home-dwelling OA population. TRs have so far been studied mainly in controlled settings [39-49], although some studies involving OAs have been conducted in institutional settings (hospital services or senior residences) [50-58] and a few of them at home [59-63]. In particular, studies conducted with OAs at home have highlighted the benefits and issues associated with the use of TRs.

With regard to the benefits of using TRs at home, cognitively healthy users have had a positive experience [60-63]. Participants in the experiments reported good acceptance, usability, perceived usefulness [59], and reliability of the TRs [63]. In the study by Cesta et al [43] the users mentioned good social and functional acceptability of the robot without any loss of interest in its use over time. They considered the mobility, entertainment, and obstacle detection features of the robot to be satisfactory [61]. They mentioned that TRs could be beneficial for physical health, psychological well-being, social contact, and independent living [60]. In the trial carried out by Bakas et al [62], OAs showed an improvement in quality of life and sleep, as well as a decrease in depression following a TR intervention.

Elderly participants of TR studies have also mentioned some issues when experimenting with these tools at home. In the study by Gonzalez-Jimenez et al [59], some participants feared that video calls with TRs might replace real human contact with relatives and friends. They also noted that the robot was too big and too noisy and that its battery required too much energy. In another study [60], the obstacles identified to the implementation of TRs were the unsuitability of the robot’s wheels for different types of floors and a slight confusion for some users when using the handheld remote control. Concerns about operating the robot from a distance were also reported by some secondary users (eg, family members or friends). One participant with mild cognitive impairment requested the withdrawal of the robot due to the significant difficulties encountered while using it. Therefore, the authors concluded that TRs were not suitable for OAs with mild cognitive impairment. Participants also emphasized the need for good speech recognition, navigation, and self-location of TRs [61] in addition to a good internet connection to optimize their use [59,63].

Although these studies reported interesting results regarding the implementation and acceptability of TRs in OAs homes, some methodological limitations were identified, such as small sample sizes included in the studies (between 2 and 20 participants), and the fact that in some protocols the TR was tested using different implementation periods for different users within the same sample, which does not allow to have the same frequency of use of the TR and may affect its impact. Besides, the psychosocial effects of the TR intervention (eg, including outcomes such as depressive symptoms or quality of life) was measured in only 1 study [61].

To overcome the aforesaid limitations identified in the literature, the DOMIROB project aims to implement a TR and assess its impact in 60 OAs living at home for a period of 12 weeks, with the same length of implementation for all participants. The main objective of this study is to measure the impact of a TR intervention on the feeling of loneliness and social isolation of OAs living at home who may benefit from the robot for a 12-week period. We hypothesize that the use of a TR at home would reduce the feeling of loneliness and social isolation in OAs.

The experimental protocol of the DOMIROB project, inspired by the MARTA (Multidimensional Assessment of Telepresence Robot for Older Adults) model [59], allows the psychosocial and ergonomic dimensions of TRs to be examined using a multimethod longitudinal design. To avoid the risk of complex and cumbersome evaluation for the users, we have reduced the number of evaluation scales in the MARTA model and have only kept the measures for loneliness, perceived social support, depression, acceptability, usability, self-perceived health, and the effect of a device on independent living. Concerning the qualitative evaluation of the experimentation, we propose a complementary and original assessment performed using a semidirective interview inspired by the Core Model of the European Network for Health Technology Assessment (EUnetHTA) [64], which is described later.

## Methods

### Study Design

The DOMIROB protocol is a nonrandomized, quasi-experimental field trial using a multimethod and multidimensional assessment. The experimental phase of the study took place between September 2020 and February 2023. Volunteer OAs were recruited between September 2020 and August 2022 in Paris, France. This study included 60 OAs who agreed to host and use a TR in their home for a period of 12 weeks.

### Determination of Sample Size

The sample size and power calculation for this study were performed based on 1 of the main outcome measures for this study: the feeling of loneliness, as assessed with the Perceived Loneliness Scale (UCLA; version 3) [65]. From a statistical point of view, we consider that the average score for the UCLA scale, observed for people aged 65 years and over, is 31.51/80 [65]. The higher the score, the greater the perceived loneliness is evaluated. Therefore, our hypothesis aims at a decrease in the average score in the UCLA scale of 3-5 points. If we want to show a decrease of 15% in the average score on the UCLA, between the assessment done at week 0 and week 24 with a power of 0.8 and a risk α of .05, then 60 individuals should be included. A decrease in the UCLA loneliness score of 15% after a 12-week implementation of the TR is clinically relevant.

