### Objectives

#### Main Objective and Primary Outcome Measures

The main objective of this study is to measure the impact of a 12-week intervention using a TR in the home of OAs on their feeling of loneliness and social isolation. To measure the impact of TRs on the feeling of loneliness, we will use the UCLA (version 3) [65]. We will assess social isolation using the Multidimensional Scale of Perceived Social Support (MSPSS), which is a tool for measuring the perception of social support that a person has [66]. We will compare the results obtained in the assessments performed at weeks 0, 6, 12, and 24 to identify the possible decreases in the scores of the different scales at different times of the implementation of the TR at home.

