### Procedure and Time Schedule

All stages of the experimental phase are illustrated in Figure 3, which describes the different actors involved in each step of the experimental phase, its length, the eventual assessment carried out at that moment, and the respective assessment tools.

During their participation in the protocol, the participants complete 4 assessments (including scales and interviews) as shown in Table 3.

The first evaluation is performed at the time of inclusion at week 0 (ie, approximately 1 week before the implementation of the TR in the volunteers’ homes; Figure 4). A second evaluation (intermediate evaluation) is conducted 6 weeks after the beginning of the experiment at home. A third evaluation (final evaluation) is carried out at the end of the implementation phase (week 12). To conclude the participation in the protocol, the volunteers are invited to take part in a final assessment (follow-up evaluation) at week 24, approximately 12 weeks after the robot has been removed from the participants’ homes. Assessments of participants are conducted face-to-face for the inclusion, and then via the video call functionality of the Cutii robot or by telephone at weeks 6, 12, and 24. Semistructured interviews at week 12 are conducted by a psychologist and recorded using a voice recorder to be transcribed and analyzed.

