### Data Analysis

#### Quantitative Analysis (Standardized Scales)

The descriptive data for all the questionnaires will be presented in the form of both average scores and SDs. Inferential statistical analyses of the results obtained during the different evaluation weeks will then be performed. All collected data will be analyzed using the open-source statistics program Jeffreys’s Amazing Statistics Program (version 0.14.1; JASP Team). For the scores of questionnaires on social isolation (GDS, MSPSS, and UCLA), a 1-way ANOVA or its nonparametric alternative (the Friedman test) will be applied according to the result of Shapiro-Wilk normality test. Then the Mauchly test of sphericity will be performed to see if any postcorrection of the degrees of freedom has to be made so that the valid *F*-ratio can be obtained. For the questionnaires concerning the use of TRs (SUS, PIADS, and ALMERE), the Shapiro-Wilk test will be used to verify the assumption of normal distribution of data to determine whether the paired (2-tailed) sample *t* test or Wilcoxon signed-rank test will be used. It should be noted that for a better interpretation of the results of the ALMERE, the Cronbach α index will be used to ensure a proper internal consistency of the questionnaire. Similarly, the multiple linear regression will be used to determine the predictive links between different aspects presented in the ALMERE model.

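### The sample size section attaches its power to UCLA change at week 24, after the robot has gone, but justifies the effect after 12 weeks of use; no single contrast is designated

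*Protocol article*

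**What the plan says.** All references are to the Protocol article.

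- **Determination of Sample Size.** The trial is sized on one of its main outcomes, "the feeling of loneliness, as assessed with the Perceived Loneliness Scale (UCLA; version 3"). The reference mean is 31.51 out of 80, the target is a 15% fall (also given as 3 to 5 points), alpha is .05 and N is 60. The powered comparison is "between the assessment done at week 0 and week 24 with a power of 0.8". The closing sentence of the section reads "A decrease in the UCLA loneliness score of 15% after a 12-week implementation of the TR is clinically relevant".
- **Introduction.** The stated hypothesis is that using the robot at home would reduce loneliness and social isolation.
- **Main Objective and Primary Outcome Measures.** The objective is to "measure the impact of a 12-week intervention using a TR in the home of OAs" on loneliness and social isolation. The comparison is described broadly: "We will compare the results obtained in the assessments performed at weeks 0, 6, 12, and 24", looking for decreases at different times while the robot is implemented at home.
- **Procedure and Time Schedule.** Week 12 is the final evaluation, at the end of implementation. Week 24 is the follow-up evaluation, "approximately 12 weeks after the robot has been removed".
- **Quantitative Analysis.** For GDS, MSPSS and UCLA, "a 1-way ANOVA or its nonparametric alternative (the Friedman test) will be applied", with the choice made by a normality test and followed by a sphericity check.

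**The concern.** Two adjacent sentences in the sample size section place the same 15% effect at different times. One is a visit when participants have been without the robot for about 12 weeks. The other is a period of 12 weeks with it. The first concerns whether an effect lasts, the second whether having the robot changes loneliness. The article gives no reason for powering on the later visit and does not say that its main hypothesis concerns persistence.

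The analysis section does not settle the matter, because a test over four visits asks only whether any visit differs from any other.

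Three things are at stake:

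- A robot that helps while it is in the home, but whose effect fades, could fail the comparison the trial was sized on.
- A significant overall test could come from a pattern other than a fall by week 12, including worsening after removal.
- With four visits, two main outcomes and no control group, an undesignated contrast leaves room to stress the most favourable visit afterwards.

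**Working it through.** **1. Time points side by side**

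| Element | Time | Robot in the home? |
|---|---|---|
| Power statement | week 0 to 24 | removed about 12 weeks before |
| Relevance of the 15% | after 12 weeks of implementation | yes, up to that point |
| Hypothesis | use at home, no visit named | yes |
| Main objective | 12-week intervention; weeks 0, 6, 12 and 24 compared | mixed |
| Planned test | any difference among the four visits (the sphericity check implies repeated measures) | mixed |

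The Main Objective section treats all four visits as times during implementation. The Procedure section shows that week 24 is not one of them. The mismatch is in the text and needs no arithmetic.

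**2. The plan's own figure**

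Effect: 0.15 × 31.51 = 4.73 points. The article gives no SD of change, within-person correlation, sidedness or named test, so N = 60 cannot be reproduced. It can only be solved backwards.

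- Two-sided paired t, n = 60, 80% power: standardised change dz = 0.368, so SD of change = 4.7265 / 0.3677 = 12.85.
- Normal approximation: 4.7265 × √60 / (1.960 + 0.842) = 13.07.
- One-sided paired t: dz = 0.325, SD of change = 14.55.

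**3. Illustration: what persistence does to power at week 24**

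Assumptions, none from the article: the week-12 effect is 4.73 points, the SD of change is 12.85 at both visits, n = 60, and the test is a two-sided paired t. Power comes from the noncentral t distribution with 59 degrees of freedom and noncentrality f × 0.368 × √60 = f × 2.85, where f is the fraction of the effect left at week 24.

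| f | Change at week 24 (points) | Power, week 0 to 24 |
|---|---|---|
| 1.00 | 4.73 | 80% |
| 0.75 | 3.54 | 56% |
| 0.50 | 2.36 | 29% |
| 0.25 | 1.18 | 11% |
| 0 | 0 | 5% |

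The f = 0.50 row depends on the SD. Replacing 12.85 by 8, 10 or 14.55 gives about 61%, 44% or 24%, where full-effect power is 99%, 95% or 70%.

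**4. Illustration: the overall test**

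Further assumption: compound symmetry with correlation 0.5, so the within-person error variance is 12.85² / 2. Noncentrality is n × Σ(mean − grand mean)² / error variance, on 3 and 177 degrees of freedom.

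| Mean change at weeks 0 / 6 / 12 / 24 | Overall F power |
|---|---|
| 0 / −2.36 / −4.73 / −2.36 | 65% |
| 0 / −2.36 / −4.73 / −4.73 | 80% |
| 0 / −2.36 / −4.73 / 0 | 80% |
| 0 / 0 / 0 / −4.73 or +4.73 | 84% |

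The week 0 to 12 contrast has 80% power in the first three rows. The overall test therefore loses power for some patterns and not for others. The last row matters for interpretation: with no change at all by week 12, the test is equally likely to be significant for improvement or worsening at week 24.

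**The case against.** The strongest reply is that the length of the intervention is not an assessment time. The objective describes a 12-week exposure, lists week 24 among the visits compared and names none as primary; the Abstract also makes the 12-week follow-up part of the design. Sizing a trial on a lasting effect is legitimate, and an effect after 12 weeks of implementation could loosely include a later visit. This stands in part: week 12 is explicit only in the relevance sentence and is an inference for the objective. The reply does not explain why the hypothesis is about use of the robot, or why no sentence says that persistence is the aim.

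A reader might infer that the trial cannot answer its main question. The documents do not support that. UCLA is collected at week 12 (Table 3) and enters the planned analysis, and N would remain 60 under the same effect and SD.

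A reader might also infer that the plan declares three rival primary comparisons. It does not. One comparison carries a power statement, one a remark on relevance, and one is the general test; none is labelled primary. Follow-up contrasts may be set out in a full protocol or analysis plan that is not shown, so their absence here is not the fault. The objective section does state an interest in decreases. The fault is that the stated power and the stated relevance disagree on time, and the stated test does not resolve it.

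The power figures are fairly called illustrative, and the overall test is not always the weaker one, as the working shows.

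**Conclusion.** The point holds as an internal contradiction. The 80% power is attached to week 0 to 24, the clinical justification of the same effect to 12 weeks with the robot, and the planned test designates neither. A significant overall result would not by itself show that loneliness fell by week 12.

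The possible size is large but conditional: about 29% power at week 24 if half of a 4.73-point effect persists, and 5% if none does. This rests on a back-solved SD of change, equal at both visits, a two-sided paired t test and assumed persistence. If the effect persists in full, nothing is lost. The time point alone does not show N = 60 to be wrong. Nor can the 80% simply be moved to week 12, because the article does not give the inputs to reproduce it for any contrast.

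**What to change.** - **Name one primary UCLA contrast**, with a 95% CI, in the same terms in Determination of Sample Size, Main Objective and Primary Outcome Measures, and Quantitative Analysis. Within-participant change from week 0 to week 12 fits the hypothesis and the relevance sentence, with week 24 as a secondary persistence contrast. If persistence was truly intended, keep week 24 and rewrite the objective and the relevance sentence to say so.
- **Restate the power for that contrast**, giving its assumed effect, SD of change, test and sidedness, rather than carrying the 80% across.
- **Date and disclose the change.** The Results section reports 56 participants recruited and analysis under way since August 2022. The amendment should say whether outcome data had been seen when the contrast was chosen; otherwise it could itself look like selection after the fact.

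The cost is wording, a restated power figure and a disclosed amendment. No new visits or participants are needed, since UCLA is already measured at all four visits.
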